### Design

Participants will be randomised (1:1) by participant code number to a control group (CNL) or to bolus advisor use (EXP) where they will utilise an automated bolus advisor to determine prandial and correction insulin doses. Both study groups will receive intensive diabetes management with frequent assessment and adjustment of insulin therapy parameters. The study design is shown in Figure 1. Participants from both arms will be evaluated with the same scales and measures at the same time intervals over 6 months.

**Figure 1 F1:**
[figure not shown]
CONSORT Diagram.

### Procedure

EXP participants will utilise the Accu-Chek® Aviva (Roche Diagnostics, Indianapolis, USA), which incorporates an automated bolus advisor into a blood glucose meter. Users can obtain prandial and correction bolus recommendations based upon a current blood glucose value, planned carbohydrate intake and individualised therapy parameters stored in the device. The device automatically calculates the appropriate bolus for the user and stores blood glucose and meal information in an electronic diary. A previous study [24] showed that the automated bolus advisor device can assist people in achieving desired postprandial glucose control without significant hypoglycaemia.

Physicians and staff in both arms will be informed about the clinical investigational plan, including the rationale for the study, design of the study protocol, subject-related procedures, and use of evaluation questionnaires. EXP physicians and staff will receive training on using the automated bolus advisor device to set insulin parameters and download SMBG and insulin dosing data.

Approximately 50-60% of the sites (those with prior experience of CGM use) will utilise a blinded continuous glucose monitoring (CGM) device (DexCom Seven® Plus, DexCom, Inc., San Diego, California, USA), with data uploaded directly to a designated secure server. Clinicians and participants will not have access to this CGM data for the duration of the study, which will be analysed centrally to contribute to the secondary end-points of the study.

### Visit schedule

The 6-month study will consist of a screening and training period of approximately 2 weeks ± 5 days and an intervention period of approximately 24 weeks. An optional follow-up patient survey by the investigator will be administered after an additional 26 weeks following Visit 10 (End of Study) (Figure 2).

**Figure 2 F2:**
[figure not shown]
Study Visit Schedule.

#### Visit 1: screening and training (week – minus 2)

At Visit 1, investigators will confirm participants’ eligibility for the study (based on inclusion/exclusion criteria), obtain written informed consent, record demographic information, collect relevant medical history/lifestyle information, document all current medications, perform physical examinations, measure and record weight, height, blood pressure, heart rate, collect blood and urine samples for laboratory tests (HbA1c, urinalysis, chemistry panel with lipids, full blood count [FBC]) and perform pregnancy testing (for women of child bearing age). Participants will be asked to complete a questionnaire that incorporates the questions from standard psychometric instruments (See *Measures* section).

Investigators will use standardised worksheets to assess participants’ knowledge and skills relevant to MDI therapy and CHO counting. Selected Dose Adjustment For Normal Eating (DAFNE) plates will also be used in the CHO counting assessment. Deficits in MDI therapy and CHO counting skills will be documented and addressed during Visit 2.

Participants in both groups will initially receive a blood glucose meter (Accu-Chek® Nano blood glucose meter, Roche Diagnostics, Indianapolis, Indiana, USA) and will be thoroughly trained in its operation. Where applicable, investigators will connect the CGM device to subjects and provide training.

Participants will be instructed to generate 7-point glycaemic profiles (preprandial/2-hours postprandial at all meals, and bedtime) over 3 consecutive days and document their results on a standardised form that will be provided. Using the form, participants will also document details of their meals (including number of CHOs), physical exercise (intensity and duration), basal insulin doses, prandial bolus doses, and correction bolus doses over the 3-day testing period. CGM participants will be instructed to wear their device until Visit 2. This will be done in addition to completing their 3-day, 7-point glycaemic profiles.

#### Visit 2: randomisation and intensive monitoring (week – minus 1)

At Visit 2, investigators will collect participants’ bG meters, completed 3-day glycaemic profiles and CGM devices (if applicable). Investigators will upload bG meter data via the research version of the Accu-Chek® SmartPix device (Roche Diagnostics, Indianapolis, Indiana, USA). When applicable, CGM data will also be uploaded to the server. Blood glucose data will be downloaded to clinic software, using either the commercial Accu-Chek® Smart Pix device or Accu-Chek® 360˚ View diabetes management system software (Roche Diagnostics, Indianapolis, Indiana, USA), and investigators will prepare printouts to review with each participant. New adverse events (AEs) and significant adverse events (SAEs), or changes in ongoing AEs/SAEs since the last visit, will be assessed and recorded; participants’ concomitant medications will be updated.

Investigators will then conduct MDI and CHO counting training, which will be individualised to address each participant’s knowledge and/or skills deficits as identified during the MDI therapy and CHO counting assessments performed at Visit 1. Standardised checklists will be used to document participant competencies. Participants must be competent in both MDI therapy and CHO counting knowledge in order to continue in the study. Following this training, participants will be randomised to the control group (CNL) for usual care or to bolus advisor use (EXP). EXP participants will be given automated bolus advisor training materials for review at home.

#### Visit 3: training and therapy initiation (week – 0)

At Visit 3, investigators will collect participants’ bG meters, upload bG meter data to the secure server; download meter data to clinic software, and prepare printouts of bG data to review with participants. New AE/SAEs or changes to ongoing AE/SAEs since the last visit will be assessed and concomitant medications updated. Investigators will use the therapy parameter cards and instruct participants on how to use their parameters.

EXP participants will be given their automated bolus advisor device (Accu-Chek® Aviva Expert bG meter, Roche Diagnostics, Indianapolis, Indiana, USA) and instructed to discontinue use of their current bG meter. Investigators will conduct 1-hour training sessions in automated bolus advisor device use and update the devices with each participant’s new therapy parameters.

At the conclusion of the visit, all participants will receive SMBG supplies and a logbook with a 3-day glycaemic profile form. Participants will be instructed to complete the 3-day profiles one week prior to Visit 5.

#### Visit 4: telephone follow-up (week – 2)

Investigators will have the option to conduct Visit 4 as either a clinic visit or via telephone. New AE/SAEs or changes to ongoing AE/SAEs since the last visit will be assessed, concomitant medications updated, and therapy parameters will be adjusted as needed. Investigators will schedule the next visit (Visit 5) and remind participants to complete their 3-day glycaemic profile prior to that visit.

#### Visits 5 through 9 (weeks – 4 through 24)

At Visits 5 through 9, investigators will collect participants’ bG meters, upload bG meter data to a secure server; download meters to clinic software, and prepare printouts of bG data to review with participants. New AE/SAEs or changes to ongoing AE/SAEs since the last visit will be assessed and concomitant medications will be updated. At Visits 5, 7 and 9, participants’ 3-day glycaemic profiles and historic data will be collected and reviewed to adjust therapy parameters (if needed). If parameters are adjusted, participants’ automated bolus advisor devices will be updated with the new parameters. HbA1c samples will be collected at Visits 6 and 9. Additional laboratory samples will be obtained at Visit 9 for chemistry profile and lipid profile, FBC, perform dipstick urinalysis. At Visits 7 and 9, 5-day CGM data will be uploaded to the secure server. Patient questionnaires will be administered at Visits 7 and 9. Final CHO counting and MDI therapy assessments will be conducted at Visit 9.

#### Visit 10: telephone follow-up (week – 24 +48 hours)

At Visit 10, investigators will call each participant 48 hours after Visit 9 to assess and record new AE/SAEs or changes to ongoing AE/SAEs since their last visit.

#### Optional follow-up (26 weeks after Visit 10)

Investigators have the option to schedule an additional clinic visit approximately 26 weeks after Visit 10 to obtain participants’ most recent HbA1c value (performed locally as part of routine practice) and collect information about participants’ use of the automated bolus advisor device. This would include downloading data from the automated bolus advisor and documenting participants’ current insulin parameters.

### Measures

#### Primary endpoint

HbA1c: The primary endpoint of the study is glycaemic control, as assessed by change in HbA1c from baseline over 6 months specifically, looking at number of patients who achieved #62;0.5% HbA1c reduction at study end. Blood samples will be collected at screening and Visits 6 (week 11) and 9 (week 24). HbA1c analysis will be conducted by a central laboratory, using HPLC methodology (VII Turbo haemoglobin testing system, Bio-Rad Laboratories, Hercules, California, USA).

#### Secondary endpoints

*Time within Target Range:* CGM data (from 50-60% of participants) will be used to assess the change in time spent within the target bG range of 72–180 mg/dl from baseline to study end. CGM data will be collected at Visits 2 (week minus 1), 7 (week 12), and 9 (week 24).

*Other Glycaemic Measures:* Glucose data from 3-day glycaemic profiles, derived from uploaded SMBG and CGM data (when applicable) will be used to assess: 1) frequency of hypoglycaemia (within 50–72 mg/dl) and severe hypoglycaemia (<50 mg/dl with associated symptoms), overall, and by defined time blocks (12:00 a.m. to 5:00 a.m., 5:00 a.m. to 10:30 a.m., 10:30 a.m. to 4:30 p.m., 4:30 p.m. to 12:00 a.m.); 2) total number of SMBG tests and average number of SMBG tests per day and by the defined time blocks; 3) percentage of all values, preprandial values (60–0 minutes prior to meal) and postprandial values (60–180minutes after start of meal) within defined bG ranges (<50 mg/dl, 50–72 mg/dl, 72–180 mg/dl, 180–300 mg/dl, #62;300 mg/dl); 4) mean bG across the 3-day profiles and for each of the 7 time points; 5) standard deviation (SD) and coefficient of variation across the 3-day profiles; 6) Mean and SD differences between preprandial and postprandial bG values over each meal in the 3-day profiles; 7) mean amplitude of glycaemic excursions (MAGE), low bG index (LBGI), high bG index (HBGI), bG risk index (BGRI) and risk for hypoglycaemia and hyperglycaemia across the 3-day profiles. The 3-day glycaemic profile data will be collected at Visits 2 (week minus 2), 5 (week 4), 7 (week 12) and 9 (week 24).

*Automated Bolus Advisor Use and Participants’ Adjustments (EXP Group):* The frequency of participants’ bolus advisor use and subsequent adjustments based on proposed bolus amounts will be derived from data uploads of the automated bolus advisor device. Analyses will include: average number of times per day participants sought advice for mealtime and correction bolus calculation; average number of times per day participants accepted the automated bolus advisor advice; average number of insulin doses adjusted up or down per day; average number of times participants accepted the automated bolus advisor responses and adjusted boluses within specific time periods (a.m., p.m., after 10 p.m.); and differences between the average number of adjusted mealtime boluses and adjusted correction boluses.

*Participant Adherence/Use of Rule Sets:* Changes in participants’ therapy adherence to and use of rule sets in EXP participants will be derived from downloaded data obtained from automated bolus advisor devices. Adherence in CNL participants will be derived from documented therapy parameters and participants’ diaries, which are included in 3-day glycaemic profile forms. These assessments will be used to determine if participants’ adherence/use of rule sets correlates with improvement in glycaemic control. Analyses will include: average number of correctly and incorrectly used insulin-to-carbohydrate (I:CHO) rules per day for CHO intake; average number of correctly and incorrectly used insulin sensitivity factor (ISF) rules per day for bG adjustment; and number of changed I:CHO and ISF parameters compared to therapy parameters at study start (Visit 3). Data will be collected at Visits 2 (week minus 2), 5 (week 4), 7 (week 12) and 9 (week 24).

*CHO Counting:* Changes from baseline in participants’ ability to accurately count CHO will be assessed using the DAFNE plate assessment scores from Visit 1 (week minus 2) and 9 (week 24). This assessment will be used to determine if participants’ CHO counting skills correlates with improvement in glycaemic control.

*Psychosocial Outcomes*: Psychosocial outcomes including treatment satisfaction, social functioning and factors important to quality of life will be assessed using the participant questionnaire, which incorporates questions from validated psychometric instruments, as well as commonly used survey questions, to assess depression, diabetes-specific distress, diabetes self-efficacy, treatment satisfaction, health outcomes and fear of hypoglycaemia. Participant questionnaire items include: Patient Health Questionnaire depression scale (PHQ-8) [25]; Problem Area in Diabetes (PAID) [26]; Hypoglycaemia Fear Scale (HFS –II) [11];Diabetes Treatment Satisfaction Questionnaire (DTSQs, [baseline] and DTSQc [change]) [27];Gold Scale [28];and EuroQol-5 Dimensions-5 Levels measure (EQ-5D-5L) [29] (Table 2). The questionnaires will be administered at Visits 1 (week minus 2), 7 (week 12) and 9 (week 24); however, the DTSQs and DTSQc portions will be administered only at Visits 1 and 9.

**Table 2 T2:** Participant Questionnaire components

**Instrument**	**Description**	**Scoring**
*Patient Health Questionnaire 8 (PHQ-8)*[25]	Self-report measure of depression	Each of 8 items scores from 0=‘not at all’ to 3=‘nearly every day’ Major depressive disorder (PHQ-8): ≤ 4 – no significant symptoms, 5 to 9 – mild symptoms, 10 to 14 – moderate symptoms, 15 to 19 – moderately severe symptoms, ≥ 20 – severe symptoms
*Problem Area in Diabetes (PAID)*[26]	Covers a range of emotional states frequently reported in diabetes. It is primarily a measure of diabetes-specific emotional distress	Each of 20 items scores from 0=‘not a problem’ to 4=‘serious problem’ PAID summary score: 0 to 39 – no distress, 40 to 59 – mild distress 60 to 79 – moderate distress 80 to 100 – severe distress
*HFS II (Hypoglycaemia Fear Scale)*[11]	Provides an assessment of an individuals’ fear of hypoglycaemia both overall and in terms of behaviour and worry. IUsed to assess both fear of hypos and maladaptive behaviours to avoid them.	Each of 33 items scores from 0=‘never’ to 4=‘always’ Score for frequency/severity of avoidance behaviour: 0 to 36 – no/slight avoidance behaviour: 37 to 48 – moderate avoidance behaviour: 49 to 60 – frequent/severe avoidance behaviour Score for severity of worry: 0 to 43 – no/slight worry: 44 to 57 – moderate worry: 57 to 72 – frequent/severe worry
*Diabetes Treatment Satisfaction Questionnaire (baseline) DTSQs and DTSQc (change)*[27]	Baseline version measures patient satisfaction with diabetes treatment Change version developed to overcome ceiling effects with treatment satisfaction	DTSQs -- Each of 6 items scores from 0=‘very bad’ to 6=‘very good’ DTSQc -- Each of 6 items scores from −3=‘much worse now’ to 3=‘much better now’)
*Gold Scale*[28]	Categorises awareness of having reduced awareness of hypoglycaemia in patients with diabetes.	One item with score from 1=‘always aware’ to 7=‘never aware’ Impaired awareness if the Gold scale score is ≥4
EuroQol-5 Dimensions-5 Levels measure *(EQ-5D-5L)*[29]	Measures health outcomes and is applicable to a wide range of health conditions and treatments	Each of the 5 items score from 1=‘no problems’ to 5=‘unable’) EQ-5D health assessment scores from 0=‘worst health’ to 100=‘best health’)

All scales and measures used in the study will contain participant codes rather than participant identifiers. Participant identifiers will be restricted to their clinicians and senior investigators.

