## Methods/design

The Automated Bolus Advisor Control and Usability Study (ABACUS) is a 6-month, multi-center, multi-national, prospective, randomised, controlled study to assess the impact of automated bolus advisor use on clinical and psychosocial outcomes in poorly controlled (#62;7.5% HbA1c), MDI-treated T1DM and T2DM participants. The trial will be conducted at approximately 30 sites in the UK and Germany. All sites will have prior experience working with the bolus advisor prior to study initiation. All clinical investigators from the sites involved will be given detailed educational input regarding the device settings and adjustment principles (either using the automated bolus advisor or using more traditional ‘paper-copy’ (e.g., insulin-to-carbohydrate ratio/insulin sensitivity factor) at centralised study training sessions. The study protocol was approved by the National Research Ethics Service (Redditch, UK) and Ethik-Kommission der Ärztekammer Westfalen-Lippe und der Medizinischen Fakultät der Westfälischen Wilhelms-Universität Münster (Münster, Germany) and is in compliance with the Helsinki Declaration [23].

The primary outcome of the study is to determine if use of an automated bolus advisor is associated with a significant reduction in HbA1c over 6 months, compared with a group having the same diabetes educational background but with no access to an automated bolus advisor. The goal is to decrease HbA1c by #62;0.5%. Secondary outcomes include: 1) change in time spent within bG target range; 2) frequency and severity of hypoglycaemia; 3) change in magnitude of postprandial glucose excursions; 4) change in glycaemic variability parameters; 5) frequency of bolus advisor use; 6) frequency of participants’ adjustments to proposed bolus amounts; 7) self-monitoring of blood glucose (SMBG) test frequency; 8) change in participants’ therapy adherence and use of rule sets; and 9) participant self-care behaviours, and psychosocial outcomes including treatment satisfaction, social functioning and factors important to quality of life.

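### The hypoglycaemia frequencies leave out symptom-free values below 50 mg/dl, so the count can fall as readings get lower

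*Protocol article*

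**What the plan says.** The Methods/design section lists "frequency and severity of hypoglycaemia" as the second secondary outcome, and the Background hypothesises that the device reduces it. The working definition is item 1 of Other Glycaemic Measures under Secondary endpoints: "frequency of hypoglycaemia (within 50–72 mg/dl) and severe hypoglycaemia (<50 mg/dl with associated symptoms), overall, and by defined time blocks". The source for the whole numbered list is given just before it: "Glucose data from 3-day glycaemic profiles, derived from uploaded SMBG and CGM data (when applicable) will be used to assess" the items that follow.

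Item 3 of the same list classifies all, preprandial and postprandial values "within defined bG ranges (<50 mg/dl, 50–72 mg/dl, 72–180 mg/dl, 180–300 mg/dl, #62;300 mg/dl" (the #62; is a text-extraction trace of a greater-than sign). It has no symptom condition. Item 7 adds the low blood glucose index, the blood glucose risk index and a risk for hypoglycaemia, also without one.

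On the profile form, the Visit 1 section says that "participants will also document details of their meals (including number of CHOs), physical exercise (intensity and duration), basal insulin doses, prandial bolus doses" and correction doses are written down alongside the glucose results. On CGM, the Procedure section says: "Clinicians and participants will not have access to this CGM data for the duration of the study".

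**The concern.** The two categories in item 1 look like a severity ladder, but they do not cover the range below 72 mg/dl. The upper rung is defined by glucose alone. The lower rung needs glucose and symptoms together. A value that passes the glucose test for the lower rung but has no symptoms drops off the ladder; it does not stay on the upper rung.

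The measure is therefore not monotone: a participant or an arm can show fewer events because readings went lower. That matters here because fewer hypoglycaemic events is one of the benefits the trial sets out to show for an insulin-dosing aid. The trial also expects some participants not to feel low glucose, since it administers the Gold scale and states in Table 2: "Impaired awareness if the Gold scale score is ≥4". The omission would fall most heavily on those participants.

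The same frequencies are used elsewhere. Under Secondary outcome analyses they are compared between groups with simple tests. Under Primary outcome analysis the baseline frequencies are a candidate covariable in the single-adjustment models for HbA1c change, and the frequencies are correlated with HbA1c. The main two-sample comparison of HbA1c does not use them.

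**Working it through.** The plan states no figure on this point, so there is none to reproduce. The check classifies glucose values under the two rules.

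**Inputs.** Item 1: 50–72 mg/dl counts as hypoglycaemia; below 50 mg/dl counts as severe only with symptoms. Item 3: bands split at 50 and 72 mg/dl, with no symptom condition. Both are in Secondary endpoints.

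**Classification.**

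| Value (mg/dl) | Symptoms | Item 1 | Item 3 band |
|---|---|---|---|
| 35, 45, 49 | yes | severe | <50 |
| 35, 45, 49 | no | **neither** | <50 |
| 50, 60, 72 | yes or no | hypoglycaemia | 50–72 |
| 73 | yes or no | neither | above 72 |

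(Both bands name 72 as an endpoint; it is placed in the lower one here.)

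**Effect on the count.** Let *a* be the number of values in 50–72 mg/dl, *b* the number below 50 mg/dl, and *s* the share of those *b* values with symptoms recorded.

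- Item 1, both categories together: *a* + *s·b*.
- All values at or below 72 mg/dl: *a* + *b*.
- Left out of item 1: (1 − *s*)·*b*.

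Take ten readings at 55 mg/dl, so *a* = 10 and *b* = 0. Item 1 gives 10. Move the same ten to 45 mg/dl, so *a* = 0 and *b* = 10:

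- *s* = 0: 0 + 0 × 10 = 0
- *s* = 0.5: 0 + 0.5 × 10 = 5
- *s* = 1: 0 + 1 × 10 = 10

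Unless every low value has symptoms recorded, the item 1 total falls while glucose gets lower. In item 3 the ten values simply move from the 50–72 band to the <50 band at every *s*.

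**Range.** The article gives no value for *s*, so the following is an assumption across its whole range. Of every 100 values below 50 mg/dl, item 1 counts 0, 25, 50, 75 or 100 when *s* is 0, 25, 50, 75 or 100%. Item 3 counts 100 in each case.

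**Where symptoms could come from.** Item 1 names glucose uploads as its source. The form contents listed at Visit 1 do not mention symptoms. Participants cannot see CGM values, so they cannot note symptoms against a CGM reading. This bears most on the 12:00 a.m. to 5:00 a.m. block: the seven scheduled points are before and after each of three meals (3 × 2 = 6) plus bedtime (1), so no overnight test is scheduled and systematic data there depend on CGM. Adverse events are assessed from Visit 2 to Visit 10 and could hold symptoms, but the article does not link them to item 1.

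**The case against.** The strongest reply is that the readings are analysed, and in the same paragraph. A reader might infer from item 1 that symptom-free values below 50 mg/dl are ignored altogether; the document does not support that. Item 3 reports them as a percentage of values, item 7 reflects them in its indices, and a shift from 55 to 45 mg/dl would show in item 3. This stands, and it limits the point to item 1. It does not remove it: item 3 gives percentages, not frequencies, and is not described by time block, whereas item 1 is the measure that matches the named outcome.

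A reader might also infer that the trial does not record symptoms. That cannot be established. The article condenses a fuller protocol, the form is not shown, its listed contents need not be complete, and adverse event records may carry symptoms. What can be said is that the article names no symptom source for item 1. Even a complete symptom field would leave the gap, because a value truly without symptoms would still be in neither category.

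Finally, the same definition applies to both arms, and nothing in the document shows that the share without symptoms differs between them. A claim of bias towards the device would go beyond the text. The possibility of distortion remains, in favour of whichever arm has more symptom-free values below 50 mg/dl.

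**Conclusion.** The point holds in a limited form. As written, the item 1 categories are not exhaustive, and the frequency of hypoglycaemia, overall and by time block, can fall when readings move below 50 mg/dl without symptoms. That follows from the wording alone and needs no assumption. The size does need one: the loss is (1 − *s*) of the values below 50 mg/dl, from none to all of them, and the article gives nothing to narrow that range. The loss does not extend to the item 3 percentages or the item 7 indices.

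Severity is moderate. A secondary outcome is affected, along with the supporting HbA1c covariable and correlation analyses that use these frequencies. The main HbA1c comparison and the sample size are untouched.

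**What to change.** Bring item 1 into line with the item 3 ranges. In the frequencies and in each time block:

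- count all values below 50 mg/dl regardless of symptoms;
- count all values below 72 mg/dl, stating which band a value of exactly 72 belongs to;
- report values below 50 mg/dl with symptoms as a subset of the first count;
- state which record supplies the symptoms, and how symptoms are handled for values seen only on blinded CGM.

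Make the change before any comparison by group is seen, and use the same counts wherever hypoglycaemia frequency enters the HbA1c models and correlations.

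The cost is a reworded definition and about one more table row. The glucose values are already uploaded, so the first two counts need no new data. The downside is that reported low-glucose counts will be higher in both arms, which the report should explain.

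### SMBG test frequency, a named secondary outcome, is taken from 3-day profiles with an instructed 7-point schedule, so it largely measures profile compliance and strongly attenuates any arm difference in everyday testing

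*Protocol article*

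**What the plan says.** The Methods/design section of the protocol article lists "self-monitoring of blood glucose (SMBG) test frequency" as the seventh secondary outcome, with no restriction to particular days. The only operational definition is item 2 of the list headed Other Glycaemic Measures, under Secondary endpoints: "total number of SMBG tests and average number of SMBG tests per day and by the defined time blocks".

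That list opens with a sentence naming the data source for all its items: "Glucose data from 3-day glycaemic profiles, derived from uploaded SMBG and CGM data (when applicable) will be used to assess". It closes by giving the collection times: "The 3-day glycaemic profile data will be collected at Visits 2 (week minus 2), 5 (week 4), 7 (week 12) and 9 (week 24".

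The Visit 1 section sets out what happens on profile days: "Participants will be instructed to generate 7-point glycaemic profiles (preprandial/2-hours postprandial at all meals, and bedtime) over 3 consecutive days". The Design section applies this alike to both groups: "Participants from both arms will be evaluated with the same scales and measures at the same time intervals over 6 months".

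Meter data are also uploaded more widely. The section on Visits 5 through 9 has investigators "upload bG meter data to a secure server" at each of those visits, and the Visit 2 and Visit 3 sections contain similar uploads. None of these sections makes the data recorded between profiles the source for test frequency.

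**The concern.** The outcome is meant to show how often participants test. As written, it is observed only on days when the protocol tells them how often to test, and the instruction is the same in both arms and at baseline. A participant who normally tests three times a day and one who normally tests five times a day will both record about seven if they follow it. The measure then mostly tells us who completed the profile.

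This matters for interpretation. The Procedure section says the advisor's recommendation uses a current glucose reading, so the device may itself prompt more testing. Whether the advisor arm tests more in daily life is therefore something a reader will want to know when interpreting an HbA1c effect. A near-null result on profile days could be reported as no difference in testing when ordinary testing did differ. The planned two-sample t-test, and any correlation of HbA1c change with this measure, would use the same attenuated variable.

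**Working it through.** **Inputs from the protocol article**
- Profile schedule (Visit 1 section): before and 2 hours after all meals, plus bedtime, for 3 consecutive days.
- Profile collection (Secondary endpoints): Visits 2, 5, 7 and 9, so three profiles after baseline.
- Intervention period (Visit schedule): about 24 weeks.
- Per-protocol rule (Populations for analysis): at least 80% of the profile measurements.

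**Input that is assumed**
- The usual number of tests per day. The article gives none, so a range of 3 to 9 is shown.

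**Step 1: the scheduled count.** With three meals, 3 × 2 + 1 = 7 tests per day, which matches the article's 7-point profile. Over three days, 7 × 3 = 21.

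**Step 2: coverage.** Post-baseline profile days are 3 × 3 = 9. The intervention period is 24 × 7 = 168 days, and 9/168 = 5.4%. This shows how little of the period is observed; it is not in itself a bias.

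**Step 3: attenuation.** Let ordinary daily testing X be Poisson with mean m. Suppose that on profile days the schedule is followed and tests beyond it still count, so that the recorded number is max(X, 7). The expected profile-day count is

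E[max(X, 7)] = Σ max(x, 7) · P(X = x | m).

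| Usual rate m | Expected count on a profile day |
|---|---|
| 3 | 7.02 |
| 4 | 7.08 |
| 5 | 7.26 |
| 6 | 7.57 |
| 7 | 8.04 |
| 8 | 8.66 |
| 9 | 9.41 |

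For a true arm difference of 1 test per day, the difference left on profile days (from unrounded values) is:

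| Usual rates, arm v arm | Difference seen | Share lost |
|---|---|---|
| 3 v 4 | 0.07 | 93% |
| 4 v 5 | 0.17 | 83% |
| 5 v 6 | 0.32 | 68% |
| 6 v 7 | 0.47 | 53% |
| 7 v 8 | 0.62 | 38% |
| 8 v 9 | 0.74 | 26% |

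Counting tests on ordinary days would recover the full difference of 1.

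**Step 4: the per-protocol rule.** 80% of 21 is 16.8, so at least 17 measurements are needed, and 17/3 = 5.7 per day. Scheduled form entries in the per-protocol set therefore lie between 5.7 and 7.0 per day. This bounds only the scheduled entries. Meter counts can exceed 7, and the article places its efficacy analyses on the intention-to-treat population, so the range does not bound the outcome itself.

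**The case against.** **The wording may mean all uploads.** Items 4 to 7 of the list each repeat the restriction to the 3-day profiles; items 1 to 3, including test frequency, do not. Item 3 refers to all values and uses time windows around meals. The restriction in items 4 to 7 would be redundant if the opening sentence already applied to everything. This makes the intention uncertain. It does not override the opening sentence, which names the profiles as the source for the whole list, or the closing sentence, which gives only profile collection times. The next paragraph, on bolus advisor use, names device uploads as its source, so the authors stated a different source where they wanted one.

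**The article condenses a fuller document.** A counting window can be left to the full protocol or SAP, and silence would be no finding. Here the article is not silent: it states a source, and that source does not suit the outcome.

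**Testing is not fixed at seven.** A reader might infer that profile-day counts are set by the protocol and conceal every real difference. The documents do not support this. Seven is an instructed schedule and not a cap, and the data come from uploaded readings, so missed and additional tests would show. Nor are the time-block counts wholly dictated by the schedule: the block from midnight to 5 a.m. would ordinarily contain no scheduled point, so counts there come mainly from unscheduled tests. This objection stands, and it is why the claim is strong attenuation and not complete masking.

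**The primary result is untouched.** A reader might also infer that the HbA1c comparison is biased. It is not. In a randomised comparison, extra testing prompted by the device is part of the device's effect. Everyday behaviour in the advisor arm is also partly visible, because requests for advice per day come from device uploads. That does not supply a count in the control arm, so the between-arm question remains.

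**Conclusion.** The point holds as a mismatch between a named secondary outcome and its stated data source. Followed as written, the measure largely reflects compliance with the profile. Under the assumed model, roughly 7% to 32% of a true difference of 1 test per day remains when both arms usually test 3 to 6 times a day, rising to about 74% at 8 v 9.

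These figures rest on three assumptions: the usual rates, which the article does not give; Poisson variation; and full adherence to the seven points with extra tests still counted. Poorer adherence would change the figures, and part of what was then seen would be a difference in profile completion.

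The consequence is confined to the between-arm comparison of test frequency and its use in interpreting an HbA1c effect. The primary analysis, its power and its error rate are unaffected. It should be corrected, since the data needed are already being collected.

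**What to change.** In the Secondary endpoints section, take test frequency out of the list governed by the 3-day profiles. State that the total, the daily average and the time-block counts are derived from all meter data uploaded between visits, with days of meter use as the denominator and the 3 profile days excluded. Report profile-day counts separately, by arm, as profile completion. If all uploads were intended from the start, the same statement removes the ambiguity.

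The cost is one or two sentences and some programming; no new data are needed, because meter uploads are planned at Visits 2, 3 and 5 to 9. The drawback is a short baseline window. Visits 1 and 2 are about one week apart, so removing 3 profile days leaves about 7 − 3 = 4 days, and the baseline rate will be imprecise.
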